### Sample size calculations

#### Perioperative mortality

The primary outcome measure is perioperative death. The primary efficacy parameter is the OR comparing FEVAR with both open repair and off-label EVAR. For OSR, conservative estimate of 8% perioperative death might be expected, and a reduction to 4% could be considered clinically relevant, which is equivalent to an OR of 0.48 (based on NVR 2015 report^21^ and GLOBALSTAR registry^22^). This effect is slightly larger than that noted in randomised controlled trials of standard infrarenal aneurysm repair.^5^ A Bonferroni adjusted two-sided alpha level of 0.025 is used. Based on these assumptions, collecting data on 2000 patients will ensure a power in excess of 80% if the allocation between treatments is relatively equal and should be preserved above 70% even if one treatment strategy is used twice as much as the other two.

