#### Stratified comparative analysis for perioperative mortality and identification of risk factors

Based on the best available estimates, it is anticipated that 120 events (perioperative deaths) will be available if 2000 patients are included in the study. The aim is to identify anatomical/physiological characteristics for which there is a differential effect on patient outcome depending on the treatment strategy employed. We plan to use multivariable models which include propensity scores as continuous covariates, adjusted for appropriate confounding variables and including interaction effects with treatment effect. Using the statistical rule of thumb of 10 events per variable, approximately 12 variables can be included in any single model. If, for example, a two-level factor is to be investigated, main effects and interaction effects and a covariate of propensity scores will account for six variables, allowing for a further inclusion of other confounding variables as required.

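### With 2000 patients and a 2:1:1 split, power is about 66%, not above 70%, for a primary comparison that excludes the doubled strategy

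*Protocol article*

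**What the plan says.** The protocol article, under Sample size calculations (Perioperative mortality), defines two comparisons: "The primary efficacy parameter is the OR comparing FEVAR with both open repair and off-label EVAR". One event rate is given, for open repair: "For OSR, conservative estimate of 8% perioperative death might be expected". The target is set against it: "a reduction to 4% could be considered clinically relevant, which is equivalent to an OR of 0.48". The two comparisons share the error rate: "A Bonferroni adjusted two-sided alpha level of 0.025 is used".

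Two power statements follow. With near-equal use of the strategies, "collecting data on 2000 patients will ensure a power in excess of 80% if the allocation between treatments is relatively equal". With unequal use, power "should be preserved above 70% even if one treatment strategy is used twice as much as the other two". The second statement does not say which strategy is doubled.

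The next section, on stratified analysis and risk factors, expects that "120 events (perioperative deaths) will be available if 2000 patients are included in the study". The article gives no perioperative death rate for off-label EVAR and no expected split between strategies. Under Methods (Routinely collected data) it anticipates about 3000 eligible patients from about 8000 scans.

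**The concern.** The 70% statement is unrestricted, so it should hold for both primary comparisons whichever of the three strategies is doubled. A 2:1:1 split of 2000 is 1000/500/500. If the doubled strategy is outside a comparison, that comparison has 500 patients per group, against about 667 per group under equal allocation. A drop of that size from a starting point of about 80% need not stop above 70%.

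The affected cases are not remote. The Introduction reports substantial use of off-label standard EVAR. If EVAR were the doubled strategy, the comparison that loses power would be FEVAR v OSR, the only one for which a control rate is given.

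The second issue is that the power claim is worded for both comparisons but rests on the OSR rate alone. A reader weighing a non-significant FEVAR v EVAR result could credit it with about 80% power, for which the article gives no basis.

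**Working it through.** **Inputs.** p1 = 0.08, p2 = 0.04, two-sided alpha 0.025 (z = 2.241), N = 2000 and three strategies, all from the article. It names no test. I use the pooled normal approximation for an unadjusted comparison and then vary the test.

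**Formula.** Power = Φ[(|p1 − p2| − z·SE0) / SE1], where SE0 = √[p̄(1 − p̄)(1/n1 + 1/n2)], SE1 = √[p1(1 − p1)/n1 + p2(1 − p2)/n2], and p̄ is the pooled rate.

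**Step 1: effect size.** (0.04/0.96)/(0.08/0.92) = 0.479, which agrees with the stated OR of 0.48.

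**Step 2: equal allocation, 667 v 667.** p̄ = 0.06, SE0 = √(0.1128/667) = 0.01300, SE1 = √(0.1120/667) = 0.01296. Power = Φ[(0.04 − 0.02915)/0.01296] = Φ(0.837) = 79.9%. Other methods give 80.1% (unpooled), 78.1% (log odds ratio) and 80.6% (exact chi-square). The article's 80% is reproduced to within rounding and choice of test.

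**Step 3: 2:1:1, doubled strategy inside the comparison.**
- Comparator doubled, 1000 v FEVAR 500: p̄ = 100/1500 = 0.0667, SE0 = 0.01366, SE1 = 0.01226, power = Φ(0.765) = 77.8%.
- FEVAR doubled, comparator 500 v 1000: p̄ = 80/1500 = 0.0533, SE0 = 0.01231, SE1 = 0.01362, power = Φ(0.911) = 81.9%.

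Across test variants these run from about 74% to 85%. The 70% claim holds here.

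**Step 4: 2:1:1, doubled strategy outside the comparison, 500 v 500.** SE0 = √(0.1128/500) = 0.01502, SE1 = √(0.1120/500) = 0.01497. Power = Φ[(0.04 − 0.03367)/0.01497] = Φ(0.423) = 66.4%.

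| Test, 500 v 500 | Power |
|---|---|
| Pooled | 66.4% |
| Unpooled | 66.7% |
| Log odds ratio (Wald) | 64.5% |
| Arcsine | 67.7% |
| Exact chi-square | 67.1% |
| Fisher | 62.1% |
| Continuity-corrected | 61.4% |

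None reaches 70%. That would need 539 per group, or 4 × 539 = 2156 in total at 2:1:1. Only an alpha of 0.05, which the plan does not use, would lift the pooled figure above 70% (to 76.0%). Reading the sentence as twice the other two combined (about 1333/333/333) makes matters worse: 47.3% for the two smaller groups.

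**Step 5: larger totals.** At 3000, the two smaller groups are 750 v 750: 84.7% pooled, about 83% by log odds ratio. At 30% of 8000 = 2400 they are 600 v 600: about 75% pooled, 73% by log odds ratio.

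**Step 6: FEVAR v off-label EVAR.** No EVAR rate is stated. With FEVAR at 4% and 667 v 667:

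| Assumed EVAR rate | Power |
|---|---|
| 5% | 9% |
| 6% | 29% |
| 7% | 56% |
| 8% | 80% |

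**Step 7: do the 120 expected deaths fix the EVAR rate?** Taking OSR at 8% and FEVAR at 4% as true rates, EVAR rate = (120 − 0.08·n_OSR − 0.04·n_FEVAR)/n_EVAR.
- Equal groups: (120 − 53.3 − 26.7)/667 = 6%.
- OSR doubled: (120 − 80 − 20)/500 = 4%.
- FEVAR doubled: (120 − 40 − 40)/500 = 8%.
- EVAR doubled: (120 − 40 − 20)/1000 = 6%.

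The implied rate ranges from 4% to 8% with the split, so the 120 deaths do not determine it.

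**The case against.** The best defence is that the slip is small and unlikely to matter. Three possible doubled strategies and two comparisons make six cases. With the 8% v 4% contrast, four meet the claim and two miss it by about 4 points. The sentence is also hedged. Eligible patients enter without further selection, and both the 3000 anticipated and the 2400 implied by the 30% lower figure exceed the 2156 needed. This stands, and it limits the severity. It does not make the sentence right, because the sentence is tied to 2000 patients.

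A reader might go further and infer that FEVAR v EVAR has only 29% power on the plan's own figures, by combining 8%, 4% and 120 deaths. The documents do not support that. The 4% is a clinically relevant target, not a forecast for FEVAR. The 120 deaths appear in a different section, to budget model variables. Equal groups are a further assumption, and other splits give other EVAR rates. Lower power at a difference smaller than the design difference is true of any study and is not an arithmetic error. What remains is that no EVAR rate is given.

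A reader might also infer that the equal-allocation statement is wrong. It is borderline (78.1% to 80.6% by the methods in Step 2), and about 80% is a fair description.

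Finally, nothing in the article proposes to read non-significance as equivalence, and the Data analysis plan already reports the OR with a 97.5% CI.

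**Conclusion.** The unequal-allocation statement is wrong as written. At 2000 patients, 8% v 4% and two-sided alpha 0.025, a 2:1:1 split leaves about 66% power (61-68% by test) for the comparison that excludes the doubled strategy. Only doubling FEVAR keeps both primary comparisons above 70%, and for FEVAR v EVAR even that assumes an EVAR rate of 8%. The result rests on an unadjusted two-group comparison and an exact 1000/500/500 split.

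Power for FEVAR v off-label EVAR has no stated basis. The 29% is one scenario in a range of 9% to 80% for EVAR rates of 5% to 8%, not the plan's figure.

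Severity is minor to moderate. The shortfall is about 4 points, it disappears at the patient numbers the article anticipates, and no analysis or alpha level changes.

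**What to change.** Replace the two power statements with: about 80% with equal groups; in a 2:1:1 split of 2000, about 66% for the two smaller groups and above 70% for comparisons that include the larger one. Alternatively, quote power at the anticipated 3000 (about 83-85% for 750 v 750). The equal-allocation figure needs no change beyond saying about 80%.

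Add that these figures apply to FEVAR v off-label EVAR only if EVAR mortality is 8%, and show power over a range of assumed EVAR rates, as in the Step 6 table.

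The cost is a few sentences and a slightly less favourable stated power. No patients, data or analyses are added.

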#### Stratified comparative analysis for perioperative mortality and identification of risk factors

Based on the best available estimates, it is anticipated that 120 events (perioperative deaths) will be available if 2000 patients are included in the study. The aim is to identify anatomical/physiological characteristics for which there is a differential effect on patient outcome depending on the treatment strategy employed. We plan to use multivariable models which include propensity scores as continuous covariates, adjusted for appropriate confounding variables and including interaction effects with treatment effect. Using the statistical rule of thumb of 10 events per variable, approximately 12 variables can be included in any single model. If, for example, a two-level factor is to be investigated, main effects and interaction effects and a covariate of propensity scores will account for six variables, allowing for a further inclusion of other confounding variables as required.

#### Long-term survival; all-cause mortality

Estimated survival rates at 1, 2 and 4 years are 90%, 80% and 70%, respectively. All patients will have a median of 5-year follow-up after entering the study. It is approximated that 2000 patients should then contribute approximately 550 events (all-cause mortality after 30 days/discharge). As the study is not designed to identify a difference in long-term overall survival, no power calculation is provided to detect some minimum clinically relevant difference. Instead, assuming the difference between two treatment arms to be measured using a log HR, it is estimated that from 550 events, an SE of approximately 0.085 will be observed. This translates to a 95% CI of length of approximately 0.34. Here, an HR smaller than 0.71 or larger than 1.40 will be shown to be significant at a 5% level.

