## Introduction

Approximately 4000 individuals undergo elective repair of an abdominal aortic aneurysm (AAA) each year in the UK^1^ with the intention of preventing premature death from aneurysm rupture. The two distinct repair methods used, open surgical repair (OSR) and endovascular aneurysm repair (EVAR), each have unique advantages and disadvantages. EVAR is safer within the perioperative period, but less durable in the years to follow compared with OSR. Treatment costs also differ between the two methods.

The complexity of aneurysm repair depends mainly on anatomical detail relating to the segment of undilated aorta between renal arteries and the aneurysm, referred to as the aneurysm ‘neck’. Ideal aneurysm neck has normal diameter in cross-section which is uniform along its length with little angulation, thrombus or calcification. Infrarenal aneurysms with at least 10–15 mm length of ideal aneurysm neck are amenable to OSR with aortic occlusion clamp below the renal arteries. Such anatomy also allows standard EVAR within ‘Instructions for Use’ (IFU) defined by manufacturers of stent-grafts implanted during EVAR. Some 40%–60% of aneurysms fall within this category^2–4^ and there is a wealth of comparative effectiveness evidence relating to such patients.^5 6^ The remainder, whose aneurysm neck is too short (commonly called ‘juxtarenal’) or otherwise unsuitable for standard EVAR within IFU (on-label device use), are pragmatically referred to as having a ‘complex aneurysm’.

OSR of complex aneurysms involves aortic occlusion clamps at a variety of levels; below the renal arteries (infrarenal), below the superior mesenteric artery (suprarenal) or above the coeliac artery (supravisceral or supracoeliac) with increasing levels of physiological burden and technical difficulty as the clamp level moves higher. Complex aneurysms also call for advanced EVAR techniques such as fenestrated EVAR (FEVAR), and EVAR with adjuncts (including chimneys and endoanchors),^7^ all of which are more complex than standard EVAR. Standard EVAR outside IFU (off-label standard EVAR) is also used in routine clinical practice to treat complex aneurysms.

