Endovascular treatments are associated with greater cost than OSR due to the cumulative costs of the stent-grafts, ancillary devices, postoperative surveillance and re-intervention. National Health Service (NHS) clinical service commissioners have noted an increasing demand for FEVAR in the absence of evidence regarding clinical effectiveness identifying which patients would benefit from this procedure and whether the substantial cost associated with the technique is an appropriate use of NHS resources. Prohibitive cost and lack of experience with FEVAR in many arterial centres have concomitantly led to a substantial use of off-label standard EVAR in complex neck anatomy, an intervention that is known to have poorer long-term results compared with on-label EVAR.^17^ The National Institute for Health Research Health Technology Assessment (NIHR HTA) Programme has commissioned this comparative research study in order to resolve this NHS decision problem.

The primary aim of UK COMPlex AneurySm Study (UK-COMPASS) is to answer the research question identified by the NIHR HTA Programme: ‘What is the clinical and cost-effectiveness of strategies for the management of juxtarenal AAA, including fenestrated endovascular repair?’ The five objectives of this study are shown in table 1.

**Table 1 T1:** The UK-COMPASS objectives

Objective 1	To compare different treatment strategies for their perioperative mortality and morbidity, corrected for confounding physiological and anatomical characteristics, in order to account for baseline risk and indication biases.
Objective 2	To identify whether particular physiological and/or anatomical baseline characteristics are associated with better clinical outcomes or better health economic efficiency using one or other treatment strategies.
Objective 3	To compare different treatment strategies in terms of overall survival and in terms of treatment failure in the long-term follow-up (stent-graft-related complications, secondary interventions, aneurysm-related mortality).
Objective 4	To perform cost-effectiveness analyses from NHS and personal social care perspective to establish incremental cost-effectiveness ratios, comparing different treatment strategies in terms of cost per incremental gain in and quality-adjusted life years.
Objective 5	To establish the clinical and cost utility of FEVAR and alternatives, in patients who are considered physiologically unfit for OSR, and to compare these against medical management.

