#### Site-reported data

Quality of life (QoL) data prospectively reported by consenting patients (both operated and medically managed) from participating arterial centres in England will supplement the routinely collected data. Recruitment will be undertaken between 1 November 2017 and 31 December 2022, with follow-up until 31 December 2023.Baseline clinical data: participating centres will report baseline health and demographic data for patients recruited to the QoL aspect of the study.

Primary outcome measures are perioperative mortality, late all-cause mortality and late aneurysm-related mortality.

Secondary outcome measures are perioperative complication rates (including organ system complications, infections and complications specific to stent-grafts), perioperative secondary interventions, length of stay, intensive care usage, late complication rates (including complications specific to stent-grafts, renal failure/dialysis, aneurysm complications, infection, incisional hernia), late secondary intervention and health economic measures including incremental cost-effectiveness ratio in terms of cost per incremental gain in quality-adjusted life years.

All primary and secondary outcome measures except the health economic measures will be derived solely from the routinely collected data sources (HES, NVR and imaging). The health economic outcomes will be derived from a combination of routinely collected data sources (HES) and site-reported data sources (QoL collection).

All interventions that have been used in the study population will be compared as numbers allow. We anticipate methods of repair to include open surgery (OSR) with a variety of clamp levels (infrarenal, suprarenal or supravisceral), FEVAR, off-label use of standard EVAR and EVAR with adjuncts (including chimneys and endoanchors).

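### Objective 3 promises overall survival, but no stated survival endpoint counts all deaths from the operation, so the late hazard ratio alone will not give the net survival effect

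*Protocol article*

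**What the plan says.** Table 1 of the protocol article gives Objective 3 as "To compare different treatment strategies in terms of overall survival and in terms of treatment failure in the long-term follow-up".

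The outcome list, in the overview of the site-reported data stream, reads: "Primary outcome measures are perioperative mortality, late all-cause mortality and late aneurysm-related mortality". All-cause death measured from the operation is not among the primary or secondary outcomes.

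Under Sample size calculations, the paragraph on long-term survival gives these inputs: "Estimated survival rates at 1, 2 and 4 years are 90%, 80% and 70%, respectively" and "All patients will have a median of 5-year follow-up after entering the study". It then expects 2000 patients to yield "approximately 550 events (all-cause mortality after 30 days/discharge"), and derives a standard error of about 0.085 for the log HR and a 95% CI about 0.34 long. The same paragraph names the endpoint overall survival: "As the study is not designed to identify a difference in long-term overall survival, no power calculation is provided".

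Two other statements bear on the point. The Introduction says of standard repair that "EVAR is safer within the perioperative period, but less durable in the years to follow compared with OSR". The perioperative sample size assumes 8% deaths with open surgical repair (OSR) and a reduction to 4% as clinically relevant.

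**The concern.** The objective and the endpoint do not match. Overall survival ordinarily counts every death from the time origin. The endpoint carrying that name here counts only deaths after an early boundary, and the outcome list makes the same split.

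The deaths left outside are those on which the arms are planned to differ. Surviving the perioperative period is itself partly a result of the treatment, so a comparison that starts afterwards is conditional on a consequence of treatment. It answers a legitimate question about durability among early survivors, but not which strategy leaves more patients alive at a given time. If the early effect favours one strategy and the late effect the other, as the Introduction expects, the two questions can have different answers.

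The boundary adds a smaller difficulty. The expression 30 days/discharge is not one fixed time. Discharge can depend on the procedure, and length of stay is itself a listed secondary outcome.

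**Working it through.** **Inputs from the protocol article**
- 2000 patients and 120 perioperative deaths, i.e. 6% (stratified analysis paragraph of the sample size section).
- Perioperative death 8% v 4% (perioperative mortality paragraph).
- Survival 90%, 80% and 70% at 1, 2 and 4 years; 550 events; SE 0.085; CI length 0.34 (long-term survival paragraph).

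**1. The plan's own precision.** For two equal arms, SE(log HR) = 2/√events.
- 2/√550 = 0.0853.
- CI length = 2 × 1.96 × 0.0853 = 0.334, or 0.34 with the multiplier rounded to 2.

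Both figures reproduce, so the stated precision is that of the late-death endpoint.

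**2. Does 550 include the early deaths?** Assume that the survival rates run from the operation and that the hazard between years 2 and 4 continues to year 5.
- Hazard = ln(0.80/0.70)/2 = 0.0668 per year.
- 5-year survival = 0.70 × exp(−0.0668) = 0.655.
- All deaths by 5 years = 2000 × 0.345 ≈ 690; less 120 gives about 570.
- Alternatively, 30% of the 2000 − 120 = 1880 early survivors: 1880 × 0.30 = 564.

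Both late-only counts are close to 550, while 690 is not. Stopping at 4 years gives 600 deaths in all and 480 late ones, so the match is supportive rather than proof. It agrees with the event definition as worded.

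**3. Share of deaths outside the endpoint.** 120/(120 + 550) = 120/670 = 18%.

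**4. Late HR against overall survival at 4 years.** Assume that the 70% runs from the operation, that 6% die early on average, and that the 8% v 4% contrast holds.
- Survival to 4 years given early survival = 0.70/0.94 = 0.745.
- OSR: 0.92 × 0.745 = 68.5%.
- FEVAR: 0.96 × 0.745^HR, where HR is the late hazard ratio, FEVAR relative to OSR.

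| Late HR | OSR | FEVAR | Late HR favours | Overall survival favours |
|---|---|---|---|---|
| 1.0 | 68.5% | 71.5% | neither | FEVAR |
| 1.1 | 68.5% | 69.4% | OSR | FEVAR |
| 1.2 | 68.5% | 67.4% | OSR | OSR |

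Break-even: HR = 1 + ln(0.96/0.92)/(−ln 0.745) = 1 + 0.0426/0.295 ≈ 1.14.

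**5. Sensitivity.** If the 70% instead applies to early survivors, a late HR of 1.0 gives 0.92 × 0.70 = 64.4% v 0.96 × 0.70 = 67.2%, and break-even is 1 + 0.0426/0.357 ≈ 1.12. At 5 years, with late death risk 550/1880 = 29.3% in the OSR arm, a late HR of 1.0 gives 65.1% v 67.9%, and break-even is again about 1.12.

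**6. Precision with all deaths counted.** 2/√670 = 0.077; CI length = 2 × 1.96 × 0.077 ≈ 0.30.

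**The case against.** The strongest reply is that the key wording is a parenthesis in a precision estimate. The article states no time origin, risk set or survival model, and a condensed article may leave these to the full protocol or analysis plan. Some wording points the other way: the events come from 2000 patients rather than from early survivors, follow-up is counted from study entry, and the Data analysis plan retains all patients in their groups. This stands to the extent that a reader might infer that early deaths are certainly removed and only survivors compared. The article does not say so; that risk set is an inference from the event definition and the outcome list. What the article does fix is the endpoint, and it does so in two places.

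Second, early deaths are not lost. Perioperative mortality is a primary outcome with its own adjusted odds ratio, and together with late mortality it accounts for all deaths. The health economic analysis plans life years gained, which may combine the two periods. This also stands. But an odds ratio for one period and a conditional HR for the next do not by themselves give the net survival comparison that Objective 3 names.

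Third, a reader might infer that the late result would commonly contradict overall survival, or that a late HR of 1.2 would do so. The figures do not support that. At 1.2 both measures favour OSR, and the late HR only makes the disadvantage look larger. Disagreement in direction needs a late HR between 1.0 and about 1.14. With the plan's SE, even the top of that range gives ln(1.14)/0.085 ≈ 1.5 standard errors, short of significance at the 5% level. The risk is a misleading estimate more than a significant result in the wrong direction.

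Finally, the plan says openly that it is not designed to detect a long-term survival difference. That explains the absence of a power calculation; it does not settle which deaths the endpoint counts.

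**Conclusion.** The concern holds as a mismatch between objective and endpoint. Objective 3 names overall survival, whereas the stated survival endpoints begin after the perioperative period. About 18% of expected deaths fall outside them, and these are the deaths on which the arms are planned to differ. On the plan's figures, equal late hazards would accompany a 3.0-point difference in 4-year survival (68.5% v 71.5%). That is largely the planned 4-point perioperative difference carried forward; it would be visible in the perioperative result but not in the late HR.

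The sizes rest on the planned 8% v 4% contrast, on the 70% running from the operation, and on a constant late HR. The alternative readings tested leave a difference of 2.8 points and a break-even late HR of about 1.12, so the conclusion does not depend on the choice. No size can be given for imbalance among early survivors or for the effect of the discharge boundary, because the documents hold no figures for either.

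**What to change.** - For Objective 3, define overall survival as all-cause death from the date of operation in all operated patients, using the linked national death data that the article already plans to obtain.
- Report adjusted survival, and differences between strategies, at fixed times, or use another summary that allows non-proportional hazards.
- Keep late all-cause mortality, labelled as a landmark analysis conditional on early survival. Replace 30 days/discharge with a fixed number of days from the operation.
- Restate the long-term precision for the all-death endpoint: about 670 events and an SE of about 0.077 on the plan's own two-arm formula.

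The cost is a wording change and one additional survival summary. No new data are needed, and precision improves slightly (SE 0.077 against 0.085).

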### Data analysis plan

Analyses will be carried out on an intention-to-treat basis, retaining all patients in the surgery group to which they are assigned irrespective of any procedural issues. The intervention groups will be OSR, FEVAR, EVAR±adjuncts (including chimneys and endoanchors). The exact treatment received will be determined by triangulation of NVR data and HES data for OSR. Patients receiving endovascular treatment will be identified from NVR data and HES data, and exact technical details of each procedure (including the use of adjuncts) will be determined through analysis of procedural images in the Corelab.

As an analysis of observational cohort data, all attempts to present a measure of efficacy free from confounding bias will be undertaken. Patients will be stratified by infrarenal neck length for analysis into three groups: 0-4 mm (juxtarenal), 5–9 mm (juxtarenal) and ≥10 mm neck length (not juxtarenal but complex based on device-specific IFU criteria). This will serve to limit anatomical heterogeneity and bias within comparisons. Additionally, patients will be stratified by physiological risk. The British Aneurysm Repair Score^23^ will be used (11 clinical parameters available from NVR data) to divide each comparison group into those that are high risk (the highest risk quartile) and the remainder as standard risk.

Statistical analyses of the primary outcome shall follow the principle of propensity score analysis. Propensity score estimation is chosen for the analysis of the primary endpoint instead of multivariable regression techniques because it is considered the most appropriate means of accounting for selection bias at the low level of perioperative death rates anticipated.^24^ Propensity scores estimate the probability of a patient being given each treatment strategy based on baseline clinical and demographic characteristics. Patients can then be stratified based on their propensity to receive each treatment strategy and an estimate of treatment effect is then obtained, which adjusts for potential selection bias in the data.

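### Late-survival precision statement: the printed hazard ratio limits of 0.71 and 1.40 use the full confidence interval length as its half-length; the stated SE gives about 0.85 and 1.18

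*Protocol article*

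**What the plan says.** All of the figures stand in one paragraph of the protocol article, under Sample size calculations, Long-term survival; all-cause mortality.

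- Events: "It is approximated that 2000 patients should then contribute approximately 550 events (all-cause mortality after 30 days/discharge").
- No power claim: "no power calculation is provided to detect some minimum clinically relevant difference".
- Effect measure: "assuming the difference between two treatment arms to be measured using a log HR".
- SE: "it is estimated that from 550 events, an SE of approximately 0.085 will be observed".
- Interval: "This translates to a 95% CI of length of approximately 0.34".
- Conclusion: "an HR smaller than 0.71 or larger than 1.40 will be shown to be significant at a 5% level".

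Two other places bear on it. The Data analysis plan sets out three groups: "The intervention groups will be OSR, FEVAR, EVAR±adjuncts (including chimneys and endoanchors"). The Perioperative mortality section sizes the same 2000 patients across three strategies and adds that power "should be preserved above 70% even if one treatment strategy is used twice as much as the other two".

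**The concern.** The SE, the interval length and the significance limits are presented as one chain, each derived from the one before. An estimate is significant at the two-sided 5% level when it lies more than half the 95% interval length from zero on the log scale. The printed limits lie about a whole length from zero, so the last link looks broken.

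The SE also raises a question. It is the value obtained when every death belongs to one of two equal arms, yet the 550 deaths come from the whole cohort and the cohort is divided among three treatments.

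This paragraph is the article's only quantitative account of what the study can show on late survival. Objective 3 compares overall survival between strategies, and the Site-reported data section of the Overview lists late all-cause mortality among the primary outcome measures. A reader who wants to know which hazard ratios the study could separate from 1 would take the wrong limits from it.

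**Working it through.** **Inputs.** From the Long-term survival section: 550 deaths from 2000 patients, SE 0.085, 95% interval length 0.34, limits 0.71 and 1.40. From the Data analysis plan: three groups. From the Perioperative mortality section: roughly equal use, or one strategy used twice as much as each of the others. From the Routinely collected data section under Methods: about 3000 patients anticipated to meet the anatomical criteria.

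**Formulas.** With D deaths in the comparison and a share p in one arm, SE(log HR) = 1/√(D·p·(1−p)), which is 2/√D at 1:1. The 95% interval length is 2 × 1.96 × SE. The two-sided 5% limits are exp(±1.96 × SE).

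**Step 1: reproduce the stated figures.**
- SE: 2/√550 = 0.0853. This agrees with 0.085.
- Length: 2 × 1.96 × 0.085 = 0.333, or 4 × 0.085 = 0.34 if 2 stands in for 1.96. This agrees with 0.34 as a full length.
- Limits: 1.96 × 0.085 = 0.167, and exp(±0.167) = 0.85 and 1.18. This does not agree with 0.71 and 1.40.
- Source of the printed limits: exp(±0.34) = 0.712 and 1.405. The full length has been used as the half-length.

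**Step 2: is it rounding?** No. At SE 0.085, a hazard ratio of 0.71 has |z| = 0.342/0.085 = 4.03 and one of 1.40 has |z| = 0.336/0.085 = 3.96. Both give p below 0.0001. For 0.71 and 1.40 to be true 5% limits, the SE would have to be 0.34/1.96 = 0.173, which at 1:1 means 4/0.173² ≈ 133 deaths rather than 550.

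**Step 3: three groups.** Assume that deaths divide in proportion to arm size.

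| Scenario | Deaths in the comparison | SE | 95% interval length | 5% limits |
|---|---|---|---|---|
| As stated: all 550 in one 1:1 comparison | 550 | 0.085 | 0.33 | 0.85, 1.18 |
| 2000 patients, three equal arms | 550 × 2/3 ≈ 367 | 0.104 | 0.41 | 0.81, 1.23 |
| 2000 patients, 2:1:1, the two smaller arms | 550 × 2/4 = 275 | 0.121 | 0.47 | 0.79, 1.27 |
| 2000 patients, 2:1:1, smaller against larger arm | 550 × 3/4 ≈ 413, split 1:2 | 0.104 | 0.41 | 0.81, 1.23 |
| 3000 patients, three equal arms, same event rate | 550 × 1.5 × 2/3 = 550 | 0.085 | 0.33 | 0.85, 1.18 |

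At 2000 patients with equal arms, the stated SE is 0.0853/0.1044 = 0.817 of the pairwise SE, so it is about 18% too small. The lower limit in that row is 0.8149, which rounds to 0.81.

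**Step 4: direction.** Using the full length as the half-length makes the limits too wide. Counting all 550 deaths in one comparison makes them too narrow. The widening dominates: every row of the table gives limits inside 0.71 and 1.40.

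**The case against.** **The limits might be minimum detectable effects.** Some power settings do land on the printed values at a two-sided 5% level: 90% power with 367 deaths, or 80% power with 275, both give about 0.71 and 1.40. The text does not support this reading. It disclaims a power calculation, ties the limits to an SE from 550 deaths, and describes them as values that will be significant.

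**The two-arm simplification is declared.** The paragraph says that it assumes two arms, and it does not list the late-survival contrasts. If FEVAR were compared with the other two groups pooled at 1:2, all 550 deaths would count and the SE would be about 0.090, with limits 0.84 and 1.19. The article states no such contrast, and 0.71 and 1.40 would still be wrong. What stands is that the three-group point is secondary.

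**The cohort may be larger.** This also stands. At about 3000 patients and the same event rate, an equal pairwise comparison holds about 550 deaths, and SE 0.085 is then right. A reader might infer that the SE is too small for every comparison the study will actually make. That goes too far: the shortfall applies to the paragraph's own planning figure of 2000.

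**Little harm is done.** A reader might infer that the article says hazard ratios between 0.71 and 0.85 cannot reach significance. It does not say so. It says that values beyond 0.71 and 1.40 will be significant, and that is true in every scenario above. The error understates precision and promises nothing that the study cannot deliver. It is still wrong to present these values as the 5% limits.

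**Conclusion.** The paragraph contradicts itself. Its SE and interval length agree with each other and imply 5% limits of about 0.85 and 1.18; the printed 0.71 and 1.40 come from using the full length as the half-length. This needs no assumption beyond the paragraph's own SE and a two-sided 5% level, which the pairing with a 95% interval implies.

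Secondarily, for 2000 patients and 550 deaths the SE is about 18% too small for a pairwise comparison of three equal groups, assuming deaths proportional to arm size. This does not produce 0.71 and 1.40; it partly offsets the slip that does. Across the scenarios worked, the lower limit lies between 0.79 and 0.85 and the upper between 1.18 and 1.27.

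The severity is minor. A reader might infer that the study is wrongly sized or that its late-survival analysis is compromised. The article does not support that: it says the study is not designed to find a late survival difference, it bases the 2000 patients on perioperative death, and no analysis or conduct decision depends on these limits. The broader list of primary outcome measures in the Overview makes the figure worth correcting but does not change this.

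**What to change.** Rewrite the end of the paragraph so that the limits follow from the SE and the number of deaths refers to a pairwise comparison. Suggested content:

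- State the assumption that deaths are proportional to arm size.
- 2000 patients, equal arms: about 367 deaths in a pairwise comparison, SE about 0.104, 95% interval length about 0.41; a hazard ratio below 0.81 or above 1.23 is significant at 5%.
- 2000 patients, 2:1:1 use, as the unfavourable case: about 275 deaths in the two smaller arms, SE about 0.121, limits 0.79 and 1.27.
- About 3000 patients, equal arms, same event rate: about 550 deaths in a pairwise comparison, SE about 0.085, limits 0.85 and 1.18.

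The cost is one corrected paragraph. Sample size, data collection, analysis and conduct stay as they are.
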